### Imaging and ulcer evaluation

Wound documentation includes a 3D camera with an AI-based wound analysis system (Curevision®, Munich, Germany) to objectively assess wound healing progress. The system analyses wound dimensions (length, width, area and depth), wound tissue (granulation, fibrin, and necrosis) in the wound bed, and provides consistent, non-operator-dependent data [35]. Wound documentation will be conducted at each follow-up visit until wound closure is confirmed. Tissue involvement, including possible osteomyelitis, is investigated by X-ray, computed tomography or magnetic resonance imaging if clinically indicated.

### Outcome monitoring

Over the 12-month follow-up period, MALE and MACE are monitored through patient interviews, focusing on vascular events (cardiac, cerebral, peripheral), amputations, infections, sepsis, hospitalisations, and all-cause mortality. For participants unable to attend on-site visits, telephone interviews are conducted to assess complications, including cardiovascular or all-cause mortality.

### Study organisation and leadership

The PTA-DFS Study is overseen by a dedicated Steering Committee responsible for the scientific aspects, study protocol adherence, and overall management. The study operates under the guidance of the Clinical Trial Unit at the University Hospital of Düsseldorf, following SOPs and ensuring Good Clinical Practice compliance. The Trial Management Committee conducts weekly meetings to manage day-to-day operations, while the Steering Committee convenes annually to evaluate study progress. A Data Monitoring Committee, including the data manager and Trial Management Committee members, oversees data quality and integrity, generating weekly reports to ensure accurate data collection and handling. AI-based tools were used solely for minor grammar and language editing; all scientific content was created and reviewed by the authors.

### Statistical methods and power calculation

The primary endpoint focuses on the difference in changes of wound area (delta wound area at first - last visit) in T2D participants after early PTA compared to individuals with standard PTA. For the primary—change in wound area after early PTA—and secondary endpoint—combined incidence of MALE and MACE—a power calculation was performed. Assuming a medium effect size (Cohen's d = 0.4), corresponding to 0.4 standard deviations of the difference in delta wound area and difference in time-to-event from baseline to last visit between groups, a sample size of n = 100 per group (total n = 200) is required to achieve 80% power at alpha = 0.05.

One explanatory variable evaluates the effect of early PTA on wound microbiome dynamics. This objective aims to measure the beta-diversity changes of the wound microbiome, assessed via whole-genome sequencing and analysed using Bray–Curtis distances. In detail, taxonomic profiles from whole-genome sequencing of the wound microbiome will be generated using bioinformatics scripts. The sequencing data, produced via the Oxford Nanopore platform [36] will be analysed with Kraken2 [37] and minimap2 [38] based on a custom database including protozoan, fungal, and viral sequences. Visualisations for comparing metagenomic composition across taxonomic levels will be generated with custom scripts. Principal coordinate analysis based on Bray–Curtis distances will assess sample clustering, with the entire workflow provided as a reproducible Snakemake pipeline [39]. Effect sizes are based on expected changes in Bray–Curtis distances for beta-diversity. Nominal variables will be compared using the Chi-Square Test and Fisher's Exact Test where appropriate. Relationships between variables (e. g., changes in wound microbiome or local microcirculation and wound healing or complications) will be assessed using partial Pearson or Spearman correlation coefficients, with adjustments for confounders and multiple testing via the Bonferroni or Benjamini–Hochberg method. The standardised mean difference (Cohen's d) will be used for power analyses due to the lack of preliminary data on changes of ulcer area and combined incidence of MALE/MACE after early PTA. Changes in beta-diversity of the wound microbiome, will be analysed using Generalised Linear Mixed models with fixed effects including treatment group, bacterial taxa, time, and random effects to account for patient variability. Interaction terms will assess differential effects between treatment groups. The secondary endpoint includes combined MALE and MACE incidence post-angioplasty. Oxygen saturation in wound environment is measured as another explanatory outcome potentially linked to wound healing. Additional outcomes will include an evaluation of risk factors such as comorbidities (severity of anaemia and stages of chronic kidney disease), severity of insulin resistance, DSPN, the duration of hospital stay and interactions with medications, including antibiotics and antithrombotic therapies. Risk endpoints include the incidence of MALE, progression of diabetic complications (e.g., neuropathy), and hospital stay duration. These will be analysed using survival analysis methods and logistic regression to evaluate risk/benefit ratios. Multiplicity will be addressed as follows: The primary outcome will be analysed at a two-sided significance level of 0.05 without adjustment. For the prespecified family of confirmatory secondary outcomes, the family-wise error rate will be controlled at 0.05 using the Holm–Bonferroni procedure. For these outcomes, raw and adjusted p-values as well as corresponding adjusted 95% confidence intervals will be reported. Exploratory outcomes will not be adjusted for multiplicity and will be clearly identified as exploratory. Safety outcomes will be reported descriptively. The interaction effects of antibiotics, PTA timing, and concomitant antithrombotic treatments on both primary and secondary endpoints will be assessed using logistic regression models and subgroup analyses. Time-to-event clinical endpoints will be analysed with Kaplan–Meier survival curves, while covariate adjustments will be incorporated using Cox proportional hazards models. Correlation analyses (partial Pearson or Spearman coefficients) will account for confounders and include multiple comparison corrections via Bonferroni or Benjamini–Hochberg adjustments. Categorical variables will be compared using Chi-Square or Fisher's Exact Tests, while continuous variables will be analysed with Wilcoxon rank-sum tests or Student's t-tests, as appropriate. Two-tailed p-values below 0.05 will be considered statistically significant. Missing data will be summarised by variable, time point, and treatment arm, and patterns of missingness will be described graphically and statistically. The primary analysis will employ multiple imputation by chained equations (MICE; m = 20 imputations) under the assumption of missing at random (MAR). The imputation model will be specified to be congenial with the planned analysis and will include treatment arm, relevant baseline covariates (e. g., age, sex, ulcer duration, ulcer size, Wagner grade, HbA1c, infection status), and outcome variables. Continuous variables will be imputed using predictive mean matching, binary variables will be analysed via logistic regression, and ordinal variables will be analysed using proportional-odds models. Estimates will be combined using Rubin’s rules. Sensitivity analyses will include (i) complete-case analysis, (ii) best–worst and worst–best case scenarios, and (iii) a delta-adjusted pattern-mixture model to assess departures from MAR and exploring missing not at random (MNAR). All statistical analyses will be performed using the R Version 4.4 and SPSS for Windows 23.0 (SPSS Inc., Chicago, IL, USA). Figures are created with GraphPad Prism, Version 7.01 (GraphPad Software, Inc., La Jolla, CA, USA) or R, and Graphical abstracts using BioRender.com.

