### Recommendations for Timing of Endovascular Therapy in Chronic-Ischemic DFU

The selected time frame for early treatment (within 48 h) was conceptually adapted from the ESC guidelines on non–ST-elevation acute coronary syndrome (NSTE-ACS), which recommend an early invasive approach within 24–72 h to prevent ischemic progression and improve outcomes. While the pathophysiology of coronary artery disease and PAD differs, the underlying principle—namely, that timely reperfusion limits tissue damage—can be applied to the context of critical limb ischemia in patients with DFS. This is supported by an observational study, which indicated that a shorter time to revascularisation (within 8 weeks) is correlated with a higher likelihood of healing in ischemic foot ulcers and limb salvage rates [40]. The time frame for follow-up visits with every 4 week examinations over 3 month is based on a post-hoc analysis suggesting that a four-week evaluation period assessing the percent change in DFU area is a robust predictor of healing at 12 weeks [41].

Limited information exists regarding the prospective outcomes of revascularisation in T2D persons with PAD and DFU. One study showed that persons with PAD who underwent revascularisation were nearly 15 times more likely to achieve wound healing compared to those who did not, with ulcer severity influencing the healing outcome [42]. Delays in revascularisation may exacerbate hypoxic conditions, favouring anaerobic bacterial proliferation, inflammation and impairing wound healing. In addition, the 48-h window represents a clinically feasible and operationally meaningful target in modern multidisciplinary diabetic foot care. Thus, this threshold balances pathophysiological urgency with realistic logistics in specialised vascular settings.

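### The primary endpoint is an absolute first-to-last change in wound area with no baseline-adjusted model stated, so ulcer size enters as noise and time of closure is invisible

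*Protocol article*

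**What the plan says.** All references are to the Protocol article.

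- **Endpoint.** Statistical methods and power calculation sets the primary endpoint as the "difference in changes of wound area (delta wound area at first - last visit) in T2D participants after early PTA", against standard PTA. No calendar time is attached to the last visit.
- **Sample size.** The same section reads "Assuming a medium effect size (Cohen's d = 0.4", expressed in standard deviations of delta wound area, and concludes that "a sample size of n = 100 per group (total n = 200") "is required to achieve 80% power at alpha = 0.05". It says there are no preliminary data on change in ulcer area.
- **Test.** The only tests named that would fit wound area are in a general line: "continuous variables will be analysed with Wilcoxon rank-sum tests or" Student's t-tests. Covariate adjustment is mentioned for the Cox models. Ulcer size appears only among the imputation covariates.
- **Measurement.** Imaging and ulcer evaluation says: "Wound documentation will be conducted at each follow-up visit until wound closure is confirmed". Table 1 marks wound area and the primary endpoint at every visit to V6.
- **Clock.** The Fig. 1 legend times follow-up visits from PTA. The elective arm has PTA within 6 weeks, the early arm within 48 h (Study design and randomisation protocol).
- **Healing speed.** Time to complete wound healing is a secondary endpoint.

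**The concern.** An absolute change in area is tied to how large the ulcer was at the start. A 1 cm² ulcer that heals completely scores 1; a 20 cm² ulcer that shrinks by 2 cm² and stays open scores 2. Among closed ulcers the score is the baseline area and nothing else, so closure at month 1 and closure at month 12 count the same. Yet the arms differ only in when PTA is done.

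Two things are at stake. First, variation in baseline size inflates the standard deviation of delta, which makes d = 0.4 hard to reach even when early PTA closes clearly more ulcers. Second, if early PTA mainly brings closure forward and most ulcers in both arms close by 12 months, the primary result can be null while the treatment works.

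**Working it through.** **1. The plan's own figure.** Two-sided alpha 0.05, 80% power, d = 0.4: n per arm = 2 × (1.960 + 0.842)² / 0.4² = 2 × 7.85 / 0.16 = 98.1, so 99. The t distribution gives 99.1, so 100. Power at 100 per arm is 80.4%. The stated 100 is right for its d.

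**2. Why d depends on ulcer size.** Let b be baseline area and f the fraction left at the end. Then delta = b(1 − f) = b × w, and w = 1 for a closed ulcer, so delta = b. Suppose w is independent of b and b is log-normal with log-SD s. In units of the mean of b, the difference in mean delta is the difference in E(w), and Var(delta) = exp(s²)·E(w²) − E(w)².

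Example with assumed inputs: closure 50% v 70%; in open ulcers f is uniform on 0.2 to 1.2, so w has mean 0.3 and mean square 0.0833 + 0.09 = 0.1733.
- E(w): 0.5 + 0.5 × 0.3 = 0.65 v 0.7 + 0.3 × 0.3 = 0.79; difference 0.14.
- E(w²): 0.5 + 0.5 × 0.1733 = 0.587 v 0.7 + 0.3 × 0.1733 = 0.752.
- s = 0.3, exp(s²) = 1.094: variances 0.220 and 0.199, SD 0.457, d = 0.14 / 0.457 = 0.31.
- s = 1.0, exp(s²) = 2.718: variances 1.172 and 1.420, SD 1.138, d = 0.14 / 1.138 = 0.12.

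The treatment effect is the same in both cases; only the spread of ulcer size has changed.

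**3. Simulation, effect on closure only.** Assumed: 100 per arm; closure 30% v 50%, 50% v 70% or 70% v 87%; f as in step 2 in both arms; 600 runs per scenario. Ranges are over the three closure pairs. The log-area model uses log(area + 0.1) with baseline log area as covariate.

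| log-SD | variance of delta explained by baseline | d on delta | t-test on delta | Wilcoxon on delta | adjusted log area |
|---|---|---|---|---|---|
| 0.3 | 15-38% | 0.28-0.32 | 52-60% | 46-62% | 82% |
| 0.5 | 32-61% | 0.21-0.25 | 32-41% | 36-47% | 77-84% |
| 0.8 | 48-77% | 0.13-0.19 | 15-29% | 27-39% | 79-82% |
| 1.0 | 56-82% | 0.10-0.15 | 12-18% | 24-33% | 77-79% |
| 1.3 | 60-85% | 0.08-0.11 | 8-13% | 19-29% | 75-79% |

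On the same data, percent change has 68-79% (t-test) or 70-86% (Wilcoxon), and comparing closure proportions 80-87%. Adjusting absolute change for baseline area reaches only 27-70%, so the scale matters as well as the covariate.

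**4. Simulation, effect on closure and on open ulcers.** Closure 55% v 75%, log-SD 0.3, 0.5, 0.8 and 1.1. The t-test on delta has 73%, 52%, 31% and 19% power; adjusted log area has 81-90%. Realised d runs from 0.35 down to 0.15, and baseline explains about 30% to 70% of the variance of delta. A repeat run with 1,500 trials per scenario used: median area 3 cm²; median residual fraction 0.5 v 0.4 with log-SD 0.6; closure rates at the median area, with log-odds falling 0.5 per unit of log area. It gave 70%, 52%, 29% and 21%, against 79-90% for log(area+1).

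**5. Speed.** Assume a hazard ratio of 1.5 for closure and 70% closure in the elective arm. Closure in the early arm is 1 − 0.3^1.5 = 83.6%, giving about 154 closures. Power for time to closure = Φ(√154 × ln 1.5 / 2 − 1.96) = Φ(0.56) = 71%. The t-test on delta has 22% at log-SD 0.5 and 8% at 1.0. Over control closure of 50-90% and log-SD 0.5-1.3, the ranges are 58-79% for time to closure, 5-24% for the t-test on delta and 7-29% for the Wilcoxon test.

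**The case against.** Much can be said for the plan, and several stronger readings fail.

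- **An unadjusted analysis is prescribed.** A reader might infer this from "The primary outcome will be analysed at a two-sided significance level of 0.05 without adjustment". That sentence concerns multiplicity. The Wilcoxon/t-test line is general, and an analysis plan not shown could name a covariate. What stands: the endpoint is fixed as an absolute change, and a covariate on that scale recovers only part of the power.
- **Delta mostly measures baseline size.** No document figure supports this as a general statement. At log-SD 0.3 baseline explains 15-38% of the variance in step 3. Choosing the Wilcoxon test softens the loss when sizes vary widely.
- **The trial ignores healing speed.** It does not: time to complete healing is secondary and area is measured repeatedly. Making it primary is a design preference. What stands is that the primary endpoint cannot register it.
- **Drop-outs are scored at their last observed visit.** The primary analysis uses multiple imputation, so this is not stated. For an ulcer that stays closed, the closure visit and V6 give the same delta. The undefined last visit matters for recurrence and for what is to be imputed.
- **The rationale contradicts the endpoint.** The Discussion says that "a four-week evaluation period assessing the percent change in DFU area is a robust predictor of healing at 12 weeks". This justifies visit spacing, not the endpoint scale; it shows that a relative scale is familiar to the authors, no more.
- **A textbook gain from baseline adjustment applies.** The variance ratio (1 + r)/2 assumes equal variances at both times, which is implausible when many wounds end at zero.
- **The result would be biased.** Type I error was 4.6-5.6% in simulation. Chance imbalance in size under blocked randomisation is noise, not bias.

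**Conclusion.** The point holds as a loss of efficiency and a gap in specification. By definition, without any assumption, every closed ulcer scores its baseline area regardless of when it closed. The sample-size arithmetic is correct; the doubt is whether d = 0.4 is attainable on this scale. In every scenario examined, d on delta was below 0.4 (0.08 to 0.35) although the treatment effect was substantial.

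The size rests entirely on assumed ulcer-size spread, closure rates and residual areas, because the document gives none of them. With closure 55% v 75%, t-test power on delta is about 73% at log-SD 0.3 and 19% at 1.1, against 81-90% for adjusted log area. That upper range also assumes that early PTA shrinks ulcers that stay open; with an effect on closure alone it is 75-84%. So the loss is moderate for similar-sized ulcers and severe for widely varying ones. A claim that most of the power is lost would hold only in the second case.

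**What to change.** Before any unblinded look, amend the primary analysis as follows.

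1. Compare log(area+1) between arms with V0 log area as covariate, and name this in place of the choice between Wilcoxon and t-test. Percent change is the alternative scale. Fix the added constant in advance; the simulations used 1 and 0.1.
2. Replace the last visit by one named visit. V6 keeps the 12-month question; a mixed model over V2-V6 is the other option. Choose one.
3. Score closed wounds as 0. Reconcile documentation until closure (Imaging and ulcer evaluation) with area at every visit to V6 (Table 1), so that recurrence is handled.
4. State whether the endpoint clock runs from PTA, as in the Fig. 1 legend, or from randomisation. Under the PTA clock, V0 to V6 can be up to 6 weeks longer in the elective arm. A fixed time from randomisation is not a scheduled visit in that arm and would need actual dates or an added visit.
5. Restate the d = 0.4 assumption on the new scale, and use the same scale for ulcer size in the imputation model.
6. Keep raw delta in cm² as a supportive analysis.

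Cost: amendment and analysis-plan wording. Baseline area is already collected, and Table 1 already schedules area to V6. Imaging after closure is extra work only if current practice stops there. The effect will be reported as a ratio or percent as well as in cm².

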## Methods/design

### Study design and randomisation protocol

The PTA-DFS Study is a prospective, monocentric, RCT including participants with T2D and ischemic DFU. Ethics approval was obtained from the local ethics committee (Heinrich Heine University, Düsseldorf, Germany) in accordance with the Declaration of Helsinki (#2022–2291). The PTA-DFS study is registered at www.clinicaltrials.gov (NCT06124586; Registration Date: 2023–08-2).

Participants will be randomly assigned in a 1:1 ratio to either the early PTA group (‘immediate PTA‘ within 48 h after leg artery stenosis (LAS) diagnosis or the elective PTA group (standard of care with PTA within 6 weeks) at the academic hospital of the Heinrich Heine University Düsseldorf, Germany, with inclusion of 200 participants within 5 years. All study participants included in the study will provide informed consent. Although the study is unblinded for both participants and physicians due to practical feasibility, blinding will be applied during the data analysis phase, with separate analysis of primary and secondary endpoints by interventionists (physicians or clinicians) and data analysts to minimise bias. After the data is unblinded, all results will be reviewed collectively. This approach aims to ensure more accurate and unbiased analysis of the primary and secondary endpoints.

Randomisation is performed using a computer-generated sequence with block randomisation to ensure unbiased allocation. The block size will be specified in advance, using blocks of 4 or 6, to maintain balance across groups throughout the study. Both groups receive standard care, with the only difference being the timing of the PTA procedure. The study is structured to ensure that, apart from the timing of PTA, all other aspects of care are consistent across both groups. All subsequent laboratory analyses will be performed in a blinded manner, without knowledge of randomisation. Aside from the timing of PTA, baseline and follow-up examinations will be conducted uniformly across both groups. To optimise recruitment efficiency, training sessions will be held with the interventional angiology staff and the diabetic foot care team, ensuring participants and staff are fully informed about study-related procedures and analyses during their state-of-the-art clinical care.

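### The 80% power stated for MALE/MACE has no valid basis, and for the wound-area endpoint it reproduces only with complete data and no crossover

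*Protocol article*

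**What the plan says.** In the protocol article, Statistical methods and power calculation, a power calculation is reported for the primary endpoint (change in wound area) and for the secondary endpoint (combined MALE and MACE). The assumed effect is a Cohen's d of 0.4, described as "corresponding to 0.4 standard deviations of the difference in delta wound area and difference in time-to-event from baseline to last visit between groups". The result is that "a sample size of n = 100 per group (total n = 200) is required to achieve 80% power at alpha = 0.05". The same section explains that a standardised mean difference was chosen because there are no preliminary data on ulcer-area change or MALE/MACE incidence after early PTA.

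The analysis for MALE/MACE is of another kind. The same section assigns time-to-event clinical endpoints to Kaplan–Meier curves and Cox models, and the text after Fig. 1 names Cox models for MALE/MACE. No hazard ratio, event rate or event count is given. For the confirmatory secondary outcomes, "the family-wise error rate will be controlled at 0.05 using the Holm–Bonferroni procedure"; the members of that family are not listed. For the primary, "The primary outcome will be analysed at a two-sided significance level of 0.05 without adjustment".

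Study design and randomisation protocol plans to include 200 participants, the same number that the power paragraph requires. The article also provides for multiple imputation of missing data, for crossover from the elective arm when wound healing is complicated, and, under Outcome monitoring, for remote contact: "For participants unable to attend on-site visits, telephone interviews are conducted".

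**The concern.** Two separate things are at issue.

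- **MALE/MACE.** A standardised difference in means does not fix the power of a Cox or log-rank comparison of censored times. With follow-up ending at 12 months, participants without an event are censored, and the information comes from the events. A stated 80% without an event count or hazard ratio therefore cannot be checked or relied on. If it stays, a null MALE/MACE result could be read as coming from an adequately powered comparison.
- **Wound area.** The calculation has less than one spare participant per arm, while the article itself foresees missing data, visits replaced by telephone calls (which cannot supply a 3D-camera measurement) and crossover. The 80% is thus a best case but is not described as one.

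**Working it through.** **1. Reproduce the stated figure.** Inputs from the article: d = 0.4, two-sided alpha 0.05, power 80%, 1:1 allocation.

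- Normal approximation: n per arm = 2(1.960 + 0.8416)² / d² = 2 × 7.849 / 0.16 = 98.1, so 99.
- Two-sample t-test (noncentral t): n = 99.08, so 100 per arm. Power at 100 per arm is 80.4%.
- A one-sided test would need 78 per arm, which does not match.

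The stated 100 per arm is therefore a two-sided, two-sample comparison of means with no allowance for loss.

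**2. Primary endpoint when fewer than 100 per arm are evaluable.** The loss rates are assumptions, since the article gives none. The figures assume that imputation recovers no information. Detectable d is approximately 0.4 × √(99.08/n).

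| Assumed missing | Evaluable per arm | Power at d = 0.4 | d detectable with 80% power |
|---|---|---|---|
| 0% | 100 | 80.4% | 0.40 |
| 5% | 95 | 78.3% | 0.41 |
| 10% | 90 | 76.1% | 0.42 |
| 20% | 80 | 71.0% | 0.45 |

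**3. MALE/MACE on its own scale.** Schoenfeld's formula for 1:1 allocation at two-sided 0.05 and 80% power: events D = 4(1.960 + 0.8416)² / (ln HR)² = 31.40 / (ln HR)². The hazard ratios below are assumptions.

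- HR 0.50: 31.40 / 0.480 = 65.3, so 66 events.
- HR 0.60: 31.40 / 0.261 = 120.3, so 121 events (about 60% of 200 participants).
- HR 0.67: 31.40 / 0.160 = 195.8, so 196 events (98% of 200).

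Inverted, the detectable HR is exp(−2 × 2.8016 / √D). The event counts are assumptions.

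| Total events | Detectable HR (80% power) | Power at HR 0.60 | Power at HR 0.67 |
|---|---|---|---|
| 80 | 0.53 | 63% | 43% |
| 60 | 0.49 | 51% | 34% |
| 40 | 0.41 | 37% | 24% |

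The power columns use Φ(|ln HR| √D / 2 − 1.960).

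**4. Can d = 0.4 be translated into a hazard ratio?** Only by adding assumptions, and the answer moves with them.

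- If 0.4 is the log hazard ratio, HR = exp(−0.4) = 0.67.
- If 0.4 is in SD units of log event time under exponential hazards (SD π/√6 = 1.283), HR = exp(−0.4 × 1.283) = 0.60.
- If 0.4 is in SD units of event-free time cut off at 12 months, again with exponential hazards, the HR is 0.35, 0.43 or 0.49 for a 12-month control-arm event rate of 30%, 40% or 50%.

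So the same d = 0.4 covers hazard ratios from 0.35 to 0.67 in these readings alone. The stated effect size does not determine the power.

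**The case against.** **The primary figure is correct.** This stands. The arithmetic reproduces, and a reader might wrongly infer that the trial fails to deliver 80% power for its primary endpoint. The article does not support that. The shortfall depends on loss and crossover rates that it does not state, and at 5% loss it is about two percentage points.

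**Missing outcomes are to be imputed, not deleted.** This also stands in part. Complete-case analysis is only a sensitivity analysis, wound area is recorded at every visit, and a wound confirmed closed has a known area. Imputation may recover some information, though in general not all, so the losses in the table are the pessimistic end for each missing rate. The effect of crossover cannot be sized: both arms receive PTA, and neither the crossover rate nor its effect on the contrast is given.

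**The MALE/MACE claim might be true.** A reader might infer that the trial can detect only very large effects on MALE/MACE. That depends on an event rate that the article does not give. With an assumed 50% control rate, 100 per arm would give 87% power for HR 0.5 and 65% for HR 0.6. On the cut-off event-free-time reading above, power exceeds 80%, but only because d = 0.4 then means at least a halving of the hazard. The claim is unsupported rather than refuted.

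**The Holm level is unknown.** The family is not listed, and Holm's later steps are less strict than its first, so no particular reduced alpha can be called the plan's own. What can be said is that the power paragraph uses 0.05, and that power is lower at any stricter step.

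**Lack of preliminary data explains the choice of d.** It does, but it does not make a means calculation valid for a censored endpoint. Without data, detectable effects across a range of event counts are the honest statement.

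**Conclusion.** The concern holds in two parts of unequal weight. The 80% power stated for combined MALE/MACE has no valid basis: it comes from a comparison of means, whereas the planned analysis depends on events and a hazard ratio, and neither is stated. This part rests on no assumed rate. The illustrations of size do: detectable hazard ratios of about 0.53, 0.49 and 0.41 assume 80, 60 and 40 events, two-sided 0.05 and proportional hazards.

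For wound area, 80% power is correct for d = 0.4 with about 100 evaluable participants per arm and no crossover. The defect is the absence of any stated margin when required and planned numbers coincide. At an assumed 5%, 10% and 20% missing, without recovery by imputation, power would be 78%, 76% and 71%. This part is a matter of stating the condition and would not alone be a serious fault.

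**What to change.** Change the text of the power paragraph:

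1. Withdraw the statement that 200 participants give 80% power for combined MALE/MACE. Give instead the hazard ratio detectable with 80% power at two-sided 0.05 for assumed event counts: about 0.53 for 80 events, 0.49 for 60 and 0.41 for 40. Add that power is lower if the endpoint is tested at a stricter Holm step.
2. Restate the primary claim as 80% power for d = 0.40 with about 200 evaluable participants (100 per arm) and no crossover. Add, labelled as assumptions without recovery by imputation, 78%, 76% and 71% power at 5%, 10% and 20% missing, or equivalently detectable d of 0.41, 0.42 and 0.45.

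The cost is a few sentences and less favourable published figures. Enrolment, endpoints and their standing in the testing plan need not change.

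### The 80% power stated for the time-to-event MALE/MACE endpoint comes from a comparison of two means and has no hazard ratio or event count behind it, so it is unsubstantiated for the planned Cox/Kaplan–Meier analysis

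*Protocol article*

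**What the plan says.** All of the sizing is in the protocol article under 'Statistical methods and power calculation'. The section covers the primary endpoint (change in wound area) and the secondary endpoint together: "combined incidence of MALE and MACE—a power calculation was performed". One effect size, Cohen's d = 0.4, serves both and is explained as "corresponding to 0.4 standard deviations of the difference in delta wound area and difference in time-to-event from baseline to last visit between groups". The result is that "a sample size of n = 100 per group (total n = 200) is required" "to achieve 80% power at alpha = 0.05". The test is two-sided: "Two-tailed p-values below 0.05 will be considered statistically significant". The reason given for using a standardised mean difference is "due to the lack of preliminary data on changes of ulcer area and combined incidence of MALE/MACE after early PTA".

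The same section plans Kaplan–Meier curves for time-to-event clinical endpoints and says that "covariate adjustments will be incorporated using Cox proportional hazards models". The Abstract and the endpoint description under 'Study design and randomisation protocol' also treat MALE/MACE as time-to-event, and the latter names Cox models. 'Outcome monitoring' sets 12 months of follow-up. The article states no HR, event proportion, expected number of events or censoring assumption for MALE/MACE.

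**The concern.** A comparison of means assumes that every participant supplies a complete value of the outcome. For MALE/MACE, a participant without an event by 12 months supplies only a censored time. The power of a log-rank or Cox comparison comes from the number of events and the HR, not directly from the number of participants. A standard deviation of time-to-event has no fixed meaning under censoring until someone says which time is meant: uncensored, log-transformed, or cut off at the end of follow-up. The printed 80% therefore does not follow from the analysis that is planned.

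What is at stake is how the lead secondary result will be read. If it is not significant, a reader may give it the weight of an 80%-powered comparison, when nobody can say from the document which effect the trial could have detected.

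**Working it through.** **Inputs from the article.** d = 0.4; 100 per group (1:1, total 200); power 80%; two-sided alpha 0.05; 12 months of follow-up; Cox/Kaplan–Meier analysis. HR and event count are not stated, so everything from step 2 on rests on assumptions named there.

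**Step 1: reproduce the stated figure.** For two means, n per group = 2(1.960 + 0.8416)² / d² = 2 × 7.849 / 0.16 = 98.1, rounded up to 99. The exact t-test gives 99.08, so 100 per group. Power at 100 per group is 80.7% (normal approximation) or 80.4% (t-test). A one-sided test would need only 78. The stated figure is thus a two-sided comparison of means, and no event count enters it.

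**Step 2: what the planned analysis needs.** Schoenfeld's formula at 1:1 allocation is events = 4(1.960 + 0.8416)² / (ln HR)² = 31.40 / (ln HR)². An HR must be supplied, so d = 0.4 has to be converted.

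**Step 3: conversions that ignore censoring (assumption: exponential times).**
- d = 0.4 on log-time, where the SD is π/√6 = 1.283: |ln HR| = 0.4 × 1.283 = 0.513, so HR = 0.599. Events = 31.40 / 0.513² = 119.3, rounded up to 120, which is 60% of 200.
- d = 0.4 on raw time with pooled SD: solve r − 1 = 0.4√((r² + 1)/2) for the ratio of means r. This gives r = 1.513 and HR = 0.661. Events = 183.1, rounded up to 184, which is 92% of 200.
- Other conversions give 153 events (concordance, HR 0.636), 197 (|ln HR| = 0.4, HR 0.670) or 278 (mean ratio 1.4, HR 0.714). The last exceeds the number of participants.

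**Step 4: power for the two HRs in step 3 at assumed event counts.** Power = Φ(√(E/4) × |ln HR| − 1.96).

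| Events E (share of 200) | HR 0.599 | HR 0.661 |
|---|---|---|
| 40 (20%) | 37% | 26% |
| 60 (30%) | 51% | 36% |
| 80 (40%) | 63% | 46% |
| 100 (50%) | 73% | 54% |

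**Step 5: a conversion that respects the follow-up limit.** Assume exponential times, all cut off at 12 months, and d = 0.4 on the resulting event-free time, with 100 per group. The HR then depends on the control event proportion. Power is by the formula in step 4.

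| Control event proportion | Implied HR | Expected events | Power |
|---|---|---|---|
| 30% | 0.35 | about 42 | 92% |
| 40% | 0.43 | about 60 | 90% |
| 50% | 0.49 | about 79 | 88% |
| 70% | 0.57 | about 120 | 86% |

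Simulated log-rank power for the same four rows is about 90%, 88%, 88% and 85%. On this reading 80% is reached, but only because the implied effects are much larger.

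**Step 6: a statement that needs no conversion.** Turning Schoenfeld's formula round, the HR detectable with 80% power is exp(−2 × 2.8016 / √E): 0.41 at 40 events, 0.49 at 60, 0.53 at 80 and 0.57 at 100, at unadjusted two-sided 0.05.

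**Step 7: multiplicity.** The article controls confirmatory secondary outcomes by Holm–Bonferroni but does not state the size of the family. If MALE/MACE belongs to it and faces a first-step level of 0.025, the 120 and 184 events of step 3 become 145 and 222. At 0.0125 they become 170 and 261.

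**The case against.** Four points can be made for the plan.

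- **The arithmetic is right.** It is: the sample size reproduces, and the primary endpoint is not in question. The fault lies in applying the figure to a different kind of endpoint.
- **The authors say that preliminary data were lacking.** That explains a generic effect size. It does not make a formula for means valid for censored data. Without an event rate, power can still be stated conditionally on events.
- **The endpoint is secondary, and confidence intervals are promised for confirmatory secondary outcomes.** This limits the harm and is why a change of wording is enough. It does not support a specific 80% claim.
- **The wording may mean event-free time within follow-up.** The phrase about time from baseline to last visit allows this, and step 5 shows that 80% would then be met with as few as about 42 events. This point stands. It does not rescue the claim, because the article states neither that reading nor the strong HRs that it implies.

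The last point also rules out a stronger conclusion. A reader might infer from steps 3 and 4 that the trial needs some 120 to 184 events, that it lacks 80% power unless most participants have an event, or that its true power is one third to two thirds. The document supports none of these. Each depends on one way of turning d into an HR and on event counts that the document does not give. 'Outcome monitoring' follows a broad set of events, including infections, hospitalisations and all-cause death, so whether events will be few or many is open.

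Nor does the defence that the article is condensed apply: the article itself prints the effect size, sample size and power and attaches them to MALE/MACE.

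**Conclusion.** The point holds as one of an unsubstantiated power claim. The 80% is correctly derived for a comparison of mean change in wound area. For MALE/MACE it is not derived for the planned analysis, because no HR or number of events is stated and d = 0.4 determines neither.

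The size of the problem cannot be fixed from the document. Under the assumed exponential conversions, the HR meant by d = 0.4 ranges from about 0.35 to 0.66 in the two main families of reading. At about 40 events, power then runs from 26% (HR 0.661) to about 92% (HR 0.35). That spread is the finding: the single printed figure covers readings with very different implications. It is a mismatch of method rather than an arithmetical slip, and it leaves the sizing of the primary endpoint untouched.

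**What to change.** In 'Statistical methods and power calculation':

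1. Limit the 80% power statement to the primary wound-area endpoint, and describe 200 participants as sized for that endpoint.
2. Remove time-to-event from the explanation of d = 0.4.
3. Replace the MALE/MACE claim with a conditional one, for example: 'The trial was not sized for MALE/MACE. With 40, 60, 80 or 100 events in total, 80% power at unadjusted two-sided 0.05 requires a true hazard ratio of about 0.41, 0.49, 0.53 or 0.57; stronger effects are required if a Holm-adjusted level applies.'

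The cost is a few sentences. No extra participants are needed, and neither conduct nor analysis changes. The drawback for the sponsor is that the statement on MALE/MACE becomes less favourable than the one now printed.
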